## Background

The total effects of an intervention (e.g., acupuncture) comprise specific and nonspecific effects [1, 2]. The specific effect is generated by characteristic and inherent components, while the nonspecific effect is generated by incidental elements [3, 4]. Acupuncture, as one of the promising non-pharmacological interventions, has been proved to be beneficial for patients in the application of evidence-based approaches [5, 6]. But the specific effect of acupuncture has been criticized. Several recent randomized trials have found that acupuncture can benefit patients while its total effect is slightly or even no better than sham acupuncture [7–9]. Some researchers attribute the effect of acupuncture to a powerful placebo effect or a nonspecific effect [10]. In addition, the greater effect has been generally observed when compared acupuncture with no treatment rather than with sham acupuncture, also suggesting that nonspecific effect can contribute to acupuncture’ benefits [11]. Therefore, the recognition of specific and nonspecific effects may be important for the selection, conduction, and optimization of acupuncture to improve clinical efficacy [12]. However, the magnitude of acupuncture’s specific and nonspecific effects, as well as their determinants, remains unclear.

Many studies have shown that the size of placebo or nonspecific effect can be influenced by psychological factors, such as expectation, emotion, awareness, and personality [13–15]. And it is worth noting that positive expectation and good doctor-patient communication are both important psychological factors on acupuncture treatment and can enhance efficacy of acupuncture [16, 17]. For instance, Kong found that expectancy could modulate the pain experience on knee osteoarthritis (KOA) patients in both acupuncture and sham acupuncture [18]. Moreover, cumulative evidence suggests that acupuncture may be accompanied by strong psychobiological responses [4]. Therefore, in our study, an emphasis will be placed on exploring the influence of psychological factors on specific and nonspecific effects of acupuncture.

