Functional magnetic resonance imaging (fMRI) can reveal the functional changes of the brain and improve our understanding about the central neurological mechanisms of acupuncture [19]. In recent years, fMRI has been applied to investigate the central regulation mechanisms of the acupuncture’s effects [20–22]. Acupuncture and sham acupuncture have relatively different brain responses in the medial frontal cortex, periaqueductal gray, and rostral ventromedial medulla during analgesia [21, 23]. Most clinical trials focus on evaluating abnormal brain activity triggered by the specific effect (acupuncture – sham acupuncture), while ignoring the modulation of nonspecific effect (sham acupuncture) on brain. Interestingly, an fMRI study has found that different pre-treatment functional connectivity characteristics can predict symptom changes for acupuncture and sham acupuncture treatment, respectively [24]. Therefore, fMRI is an appropriate method to distinguish different treatment effects of acupuncture. However, there is lack of evidence on differentiating the neurological mechanisms triggered by specific and nonspecific effects of acupuncture.

It should be mentioned that pain is one of the most important conditions for acupuncture recommended by the World Health Organization, and it is a subjective sensory condition that is sensitive to a placebo response. Knee osteoarthritis (KOA), which is a common disease with chronic pain as the main symptom, is a suitable model for investigating the specific and nonspecific effects of acupuncture. Therefore, we have designed a randomized, controlled, crossover trial to clarify the specific and nonspecific effects of acupuncture. In this study, the first objective is to evaluate the magnitude of acupuncture’s specific and nonspecific effects on treating KOA. The second objective is to assess the central neurological mechanism of acupuncture’s specific and nonspecific effects. The third objective is to explore how psychological factors affect the efficacy of acupuncture.

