## Methods

### Study design

This is a randomized, controlled, crossover clinical trial (Fig. 1). In order to accurately clarify the specific and nonspecific effects of acupuncture, a controlled, crossover trial has been designed to control the interference of individual difference (e.g., demographic characteristics, brain metrics and psychological factors) on the results. This trial has been approved by the ethical committees of Dongzhimen Hospital Affiliated to Beijing University of Chinese Medicine (NO: DZMEC-KY-2017-53-02) and registered in Chinese Clinical Trial Registry (NO: ChiCTR1900025807). The protocol will be reported following Standard Protocol Items: Recommendations for Interventional Trials (SPIRIT) statement (Additional file 1). A total of 60 patients diagnosed with KOA according to American College of Rheumatology clinical criteria will be recruited [25]. After inform consent acquisition, all patients will be randomly assigned to group A and group B based on the ratio of 1:1. The patients in group A will receive acupuncture 3 sessions per week for 4 weeks. After a 2-week washout period, the patients in group A will receive sham acupuncture 3 sessions per week for 4 weeks. The patients in group B will receive the reverse intervention process.

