#### Inclusion criteria

The inclusion criteria include the following: (1) age 45–65 years (male or female), (2) duration of chronic knee pain ≥ 6 months, (3) radiologic confirmation of knee osteoarthritis (Kellgren-Lawrence grade II or III) [26] within 12 months, (4) Numerical Rating Scale (NRS) ≥ 4 with in the past week, (5) right-handed; and (6) written informed consent.

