### Interventions

Each type of acupuncture treatment will include 12 sessions of 30-min duration over 4 weeks (3 sessions per week). The date of each patient’s treatment will be recorded, and the number of treatments received by each patient at intervention phase I and intervention phase II will be counted for monitoring adherence. The licensed acupuncturists with more than 5 years of experience with acupuncture will be trained for a standard intervention procedure before this study. Patients will be given paracetamol sustained-release tablets (Tylenol; Shanghai Johnson Pharmaceutical Co., Ltd.) as a rescue medication when they have excessive pain, and the administration of rescue medication will be recorded in detail.

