### Statistical analysis

#### Clinical data analysis

The continuous variables will be described as the mean (standard deviation) or the median. The categorical variables will be described as the percentage. The comparisons between the two groups will be analyzed by independent sample *t* test, Wilcoxon rank-sum, or *χ*^2^ test in demographic, psychological factors and other indicators. The comparison between the acupuncture and sham acupuncture will be analyzed using general liner model. Intention-to-treat analysis (ITT) will be mainly used to evaluate the efficacy of acupuncture. ITT analysis will be performed to analyze all randomized data, and last observation carried forward (LOCF) will be adopted to impute the missing values. Per protocol analysis will be used and per protocol population will include patients who complete at least 10-session acupuncture during each phase and finish 4 fMRI scans. The specific effect of acupuncture will be calculated by subtracting the effect in sham acupuncture from the acupuncture. The nonspecific effect of acupuncture will be calculated by subtracting the pre-acupuncture from the post-acupuncture in sham acupuncture phase. The data will be statistically analyzed by SPSS software.

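### The nonspecific effect is defined as the raw change during the sham phase, which also contains change that no element of the intervention produced

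*Protocol article*

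**What the plan says.** The Background gives the concept. It says that "The total effects of an intervention (e.g., acupuncture) comprise specific and nonspecific effects", and separates the two by origin: the specific part comes from the characteristic components, "while the nonspecific effect is generated by incidental elements". As a sign that a nonspecific effect exists, it notes that "the greater effect has been generally observed when compared acupuncture with no treatment rather than with sham acupuncture".

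The first objective, at the end of the Background, is to size acupuncture's "specific and nonspecific effects on treating KOA".

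The Clinical data analysis section then fixes the calculation. The specific effect is acupuncture minus sham. For the other part: "The nonspecific effect of acupuncture will be calculated by subtracting the pre-acupuncture from the post-acupuncture in sham acupuncture phase".

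The Study design section provides two conditions. Group A has acupuncture and then, after a 2-week washout, sham. "The patients in group B will receive the reverse intervention process". There is no untreated or waiting-list condition. Entry requires an NRS rating of at least "4 with in the past week", on the same scale as the primary outcome. Paracetamol is allowed "as a rescue medication when they have excessive pain, and the administration of rescue medication will be recorded in detail".

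**The concern.** A before-after change under sham is not the same thing as the effect of sham. Patients' pain may move over 4 weeks without any treatment. Patients admitted because a rating was high will on average rate lower next time. Patients may also take more or less paracetamol at week 4 than at the start of the phase. None of this is produced by an incidental element of acupuncture, yet the stated formula counts all of it as acupuncture's nonspecific effect.

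This matters because sizing that effect is half of the first objective, and because later sections build on the same quantity. The Neuroimaging data analysis section looks for brain responses tied to it, and the Oxytocin and genetics evaluation section aims to predict it. The psychological and mediation analyses relate traits and brain activity to clinical improvement. Under this definition, a patient who improves spontaneously during the sham phase counts as showing a nonspecific effect of acupuncture.

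**Working it through.** The plan gives no figure to reproduce, so the check has two parts: what the formula contains, and how large the one component that can be sized might be.

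**1. What the formula contains.** Write improvement (fall in NRS) as positive. Let S be the specific effect and N the nonspecific effect. Let H1 and H2 be natural course in phases I and II, and R the regression to the mean in phase I. Let M_sham and M_acu be the contributions of changed rescue use in the sham and acupuncture phases. With 1:1 sequences, half the patients have sham in each phase:

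- mean change under sham = N + (H1 + H2)/2 + R/2 + M_sham
- mean change under acupuncture = S + N + (H1 + H2)/2 + R/2 + M_acu
- difference = S + (M_acu − M_sham)

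Natural course and regression to the mean cancel from the difference. Rescue use enters it only if its change differs between the two treatments. In the sham-phase change taken alone, nothing cancels.

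**2. Size of R.** From the documents: entry at NRS ≥ 4 (Inclusion criteria), 1:1 allocation (Randomization and blinding), and a 2-point minimal important improvement (Clinical outcomes evaluation). Assumed, because the documents give none of these: unselected mean 4 to 6, SD 1.5 to 2, retest correlation r 0.5 to 0.8, normal ratings, the qualifying rating used as the phase I baseline, and a fresh baseline rating at phase II.

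R = (1 − r) × SD × φ(a) / (1 − Φ(a)), with a = (4 − mean)/SD

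| Case | Mean, SD, r | a | R in phase I | R/2 over both sequences |
|---|---|---|---|---|
| Low | 6, 1.5, 0.8 | −1.333 | 0.2 × 1.5 × 0.1640/0.9088 = 0.054 | 0.03 |
| Central | 5, 2, 0.6 | −0.5 | 0.4 × 2 × 0.3521/0.6915 = 0.407 | 0.20 |
| High | 4, 2, 0.5 | 0 | 0.5 × 2 × 0.3989/0.5 = 0.798 | 0.40 |

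Simulation of the central case gave 0.406 in phase I and 0.000 in phase II. With whole-number ratings from 0 to 10, simulation gave averages of 0.02 (low), 0.16 (central) and 0.33 (high). If a separate baseline rating was taken after screening, with independent measurement error, the phase I fall was about 0 in all three cases.

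Against the 2-point minimal important improvement, the continuous-scale central value is 0.20/2 = 10% and the high value 0.40/2 = 20%.

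**3. The specific effect.** In a simulation with no nonspecific effect and a specific effect of 0.50 points (mean 5, SD 2, r = 0.5, 0.7 and 0.8), the sham formula returned falls of 0.25, 0.15 and 0.10 averaged over sequences. Acupuncture minus sham returned 0.50 each time.

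**4. What cannot be sized.** The documents give no untreated course, rescue rate or paracetamol effect. Natural course and rescue use could each act in either direction.

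**The case against.** The strongest reply is that this is an openly declared working definition. The Background already uses sham acupuncture as shorthand for the nonspecific effect, and the formula is printed, so any reader can see it is the sham-phase change. This stands in part: the calculation is transparent and the flaw is one of naming and interpretation. But the shorthand repeats the equation without justifying it. The same Background defines the effect by its cause and points to a no-treatment comparison that this trial lacks. The 2-week washout is untreated time, but the formula does not use it as a comparator.

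The second reply concerns size, and most of it stands. The text shown does not say that the screening rating is the phase I baseline, and the assessment schedule is a figure that is not reproduced. Regression to the mean may therefore be negligible. Rescue use is recorded, and unpermitted analgesics lead to exclusion.

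A reader might go further and infer any of the following, none of which the documents support:

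- *The nonspecific effect will be overstated by a known amount.* The direction and size of natural course and rescue use are unknown.
- *The specific effect is biased too.* Natural course and regression to the mean cancel from that contrast.
- *A distorted share of the total effect will be reported.* No share or percentage is planned.
- *The authors assert that the sham change is psychological in origin.* The Discussion says only that it may mainly be so.

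**Conclusion.** The point holds as one about what the quantity means. An uncontrolled change under sham cannot be identified as an effect of sham needling or expectation, and no analysis of the two planned conditions can make it so. The stated rule therefore cannot deliver the nonspecific magnitude in the first objective. That conclusion does not depend on any assumed number.

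The numerical size is not known from the documents. The 0.03 to 0.40 point range covers regression to the mean only and rests entirely on the assumed inputs and on the screening rating serving as baseline. Natural course is part of any before-after change, and it remains unsized. Because the acupuncture-minus-sham contrast is untouched, this is worth correcting but does not undermine the treatment comparison.

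**What to change.** In the Clinical data analysis section, call the sham-phase difference *total change under sham acupuncture*. State that it includes natural course, and possibly regression to the mean and changes in rescue use, as well as nonspecific effects. Keep acupuncture minus sham as the specific effect.

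Use the new wording wherever the quantity is used: the first objective, the oxytocin and genetics evaluation, the neuroimaging, psychological and mediation analyses, and the conclusions.

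A table of rescue intake by treatment phase, from records already being kept, would help readers but is optional.

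The change needs no new visits, data or patients, and alters no estimate. An untreated condition would be needed to isolate the nonspecific effect. According to the Trial status section patients are already being recruited, so it is not requested. The real cost is that the trial can no longer claim to have sized a pure nonspecific effect.

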#### Neuroimaging data analysis

The resting state fMRI data will be preprocessed using the Data Processing Assistant and Resting-State fMRI (DPARSF) toolbox [48]. The preprocessing will consist of removing the first 10 volumes, slice timing, head motion correction, spatial normalization (re-sampled to 3 mm × 3 mm × 3 mm), spatial smoothing (with a 6 mm full-width half-maximum Gaussian kernel), filter (0.01–0.1 Hz), removing linear trend, and the nuisance signals (white matter signals, cerebral spinal fluid signal, and Friston 24 head motion).

After preprocessing, neuroimaging data will be evaluated by using the methods of amplitude of low frequency fluctuation (ALFF), regional homogeneity (ReHo), or functional connectivity (FC) to identify the brain responses significantly associated with the specific and nonspecific effects of acupuncture. Pearson’s correlation analysis will be used to assess the association between the brain activity and clinical variables.

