### Neuroimaging data evaluation

Many functional systems of the brain are involved in pain modulation, such as descending pain, affective, and cognitive processing systems. Resting state fMRI data will be measured to identify the neurological mechanisms of the specific and nonspecific effects of acupuncture. Functional MRI scanning will be carried out using a Siemens 3.0 Tesla scanner (Skyra, Siemens, Erlangen, Germany) equipped with a standard head coil at the Beijing Hospital of Traditional Chinese Medicine Affiliated to Capital Medical University. During the resting state fMRI acquisition, patients will be in a supine position with their eyes closed and be instructed to remain awake and avoid thinking. The resting state fMRI data will be obtained using a gradient echo planar imaging (EPI) sequence with the following parameters: whole brain, repetition time (TR) = 2000 ms, echo time (TE) = 30 ms, field of view (FOV) = 224 mm × 224 mm, flip angle (FA) = 90°, slice thickness/gap = 3.5/0.6 mm, voxel size =3.5 mm × 3.5 mm × 3.5 mm, axial slices = 32, in-plane resolution = 64 × 64, and 240 volumes. Foam pads will be used to minimize head motion and earplugs will be used to reduce noise interference. The fMRI scans will be performed at baseline and the end of 4-week treatment in each phase (Fig. 3).

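### As written, ReHo would be computed on time series already smoothed at 6 mm, so the kernel creates part of the local synchrony it measures and distorts ReHo contrasts non-linearly

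*Protocol article*

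**What the plan says.** The Neuroimaging data analysis section gives one preprocessing chain. It includes "spatial normalization (re-sampled to 3 mm × 3 mm × 3 mm") and then "spatial smoothing (with a 6 mm full-width half-maximum Gaussian kernel"), followed by filtering and removal of trend and nuisance signals. The next paragraph opens: "After preprocessing, neuroimaging data will be evaluated by using the methods of amplitude of low frequency fluctuation (ALFF), regional homogeneity (ReHo"). The metrics are joined as alternatives: "regional homogeneity (ReHo), or functional connectivity (FC").

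Nothing in the article exempts ReHo from the smoothing step or says that ReHo maps are smoothed afterwards. It gives no ReHo neighbourhood size, expected ReHo level or expected ReHo change.

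The same section plans Pearson correlations between brain activity and clinical variables. The Mediation analysis section makes brain activity the mediator between psychological factors and clinical effect.

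**The concern.** ReHo indexes how closely a voxel's time course agrees with those of its immediate neighbours. A Gaussian kernel of 6 mm full width on a 3 mm grid replaces each voxel by a weighted average of those neighbours, so adjacent voxels then share much of the same data and agree whether or not the tissue does. Part of the index becomes a property of the processing. ALFF is computed voxel by voxel and FC between regions, so neither has this circularity.

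The second objective, at the end of the Background, is the central mechanism of the specific and nonspecific effects. If ReHo is the metric chosen, the size of its change matters twice: in the contrast between conditions, and as a variable in the correlation and mediation analyses. A scale that stretches in some regions and flattens in others weakens both uses.

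**Working it through.** The article states no ReHo value, so there is no figure to reproduce. The check asks what the stated kernel does to a ReHo statistic.

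**Inputs from the article.** Kernel 6 mm full width at half maximum; grid 3 mm; band 0.01–0.1 Hz; "repetition time (TR) = 2000 ms"; 240 volumes less the first 10 = 230. Acquired voxels are 3.5 mm in plane, with slice spacing 3.5 + 0.6 = 4.1 mm (Neuroimaging data evaluation).

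**Assumptions not in the article.** ReHo is Kendall's W over a 27-voxel cube; noise is spatially independent before processing; a shared regional signal takes a fraction ρ of each voxel's variance, with ρ from 0 to 0.6.

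**Step 1: correlation made by the kernel.** The kernel SD is 6 / 2.355 / 3 = 0.849 voxel. Its discrete autocorrelation is 0.70 at one voxel and 0.25 at two. The mean pairwise correlation in a 3×3×3 cube of smoothed noise, self-pairs included, is

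[(3 + 4 × 0.7048 + 2 × 0.25) / 9]³ = (0.7021)³ = 0.346.

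Unsmoothed, it is 1/27 = 0.037. Simulation with 230 band-passed volumes and 60 runs per setting gave W = 0.037 before smoothing and 0.33 after.

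**Step 2: allowing for interpolation.** Resampling from 3.5 × 3.5 × 4.1 mm to 3 mm already correlates neighbours. With this modelled, noise W is about 0.15 before smoothing and 0.41 after. The kernel's multiple is then 0.41 / 0.15 = 2.7, against 0.33 / 0.037 = 8.9 without interpolation.

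**Step 3: effect on a true difference.** For a wide region the mean correlation is:

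- unsmoothed: ρ + (1 − ρ)/27
- smoothed: [ρ + (1 − ρ) × 0.0368 × 0.346] / [ρ + (1 − ρ) × 0.0368]

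Here 0.0368 is the factor by which the kernel reduces noise variance. At ρ = 0.05 these give 0.085 and 0.731; at ρ = 0.30, 0.326 and 0.948. A further 0.05 in ρ always moves the unsmoothed value by 0.048. It moves the smoothed value by 0.385 from ρ = 0, by 0.050 from ρ = 0.10, and by 0.010 from ρ = 0.30.

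Simulated W, in regions from a compact 27-voxel focus to a wide area:

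| Step in ρ | Unsmoothed W, approx. | Smoothed difference ÷ unsmoothed difference |
|---|---|---|
| 0 to 0.05 | 0.04 to 0.08 | 3.6–8.6 |
| 0.05 to 0.10 | 0.08 to 0.13 | 2.2–2.3 |
| 0.10 to 0.20 | 0.13 to 0.22 | 0.92–1.35 |
| 0.20 to 0.30 | 0.22 to 0.31 | 0.36–0.77 |
| 0.30 to 0.40 | 0.31 to 0.41 | 0.21–0.54 |
| 0.50 to 0.60 | 0.50 to 0.60 | 0.08–0.25 |

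The ratio crosses 1 at an unsmoothed W of about 0.15–0.25. The direction of a true difference is kept; its size is not.

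**Step 4: standardised difference.** Using within-simulation SDs, smoothing lowered it at every step for a compact focus (for example 8.4 to 4.0 for ρ 0.30 to 0.40). For wide regions it was higher at very low ρ (about 6 to 13 for ρ 0 to 0.05), about equal for ρ 0.10 to 0.20, and lower from ρ 0.20 upward.

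**The case against.** The strongest reply is that this is a condensed article. The chain is a one-sentence list, a toolbox is named, and the detailed analysis is referred to Fig. 4, which is not reproduced here. Step order for each metric could sit in a fuller imaging plan, and the team may already intend to run ReHo on unsmoothed data. That is possible, and if so one sentence settles the matter. But the point does not rest on missing detail: the article itself places smoothing in the preprocessing and the metrics after it.

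Other replies stand and limit the point. ReHo is one of three alternatives and may not be used. It is a mechanistic measure. The same chain serves both treatments. Interpolation accounts for part of the neighbour agreement, so the fix would not bring the noise floor down to 0.04.

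Three stronger readings do not hold:

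- A reader might infer that the acupuncture–sham contrast in ReHo is simply compressed. Compression occurs only above an unsmoothed W of about 0.2; below that the raw contrast is enlarged. The article gives no ReHo level to say which applies.
- A reader might infer a large loss of power. Raw differences in W do not show that. The standardised results vary with region size and synchrony, and they omit between-patient variability.
- Because "filter (0.01–0.1 Hz") is listed before "removing linear trend, and the nuisance signals", a reader might infer that unfiltered regressors put out-of-band noise back into filtered data. The article does not say that the regressors are unfiltered, and tissue signals drawn from already filtered images would be filtered too. That inference is not part of this point.

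**Conclusion.** The concern holds in limited form. If ReHo is used in the stated order, the kernel creates neighbour agreement: noise W rises from about 0.04 to 0.33, or from about 0.15 to 0.41 with interpolation. Equal true changes in local synchrony then appear as unequal ReHo changes, depending on the region's baseline synchrony. ReHo changes are not comparable across regions, and their use in the correlation and mediation analyses is weakened.

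It would be wrong to conclude that the plan manufactures a difference between acupuncture and sham. The artefact is common to both conditions and does not by itself create one. The NRS primary outcome is unaffected.

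The figures rest on the assumed 27-voxel Kendall's W and the simple signal-plus-noise model. The ratios in the table come from noise without interpolation, so the turning point near 0.2 is approximate. The point is worth correcting because the correction is cheap; it does not threaten the trial's clinical conclusions.

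**What to change.** In the Neuroimaging data analysis section, state that ReHo is computed on unsmoothed normalised data and that the resulting ReHo maps are then smoothed with the 6 mm kernel. Keep smoothing before ALFF and FC as planned. If this is already the intended procedure, a clarifying sentence is enough.

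The cost is one extra processing branch. No new scans are needed and no other part of the design changes.
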